### 2.6. Sample Size

The study was pragmatically powered with n = 20 participants per group (intervention and control) for this initial feasibility and estimation phase. The calculation assumes a two-sided α = 0.05 and a nominal power of 80%, using an ANCOVA model adjusted for baseline values and repeated measures to increase statistical efficiency. Previous exercise-based trials in PLWBC [14,15,16] have reported between-group differences of approximately 8–10 points in the EORTC QLQ-C30 Global Health Status/QoL domain, with standard deviations around 20–30 points. Based on these data, a fully powered confirmatory trial would require substantially larger samples; therefore, the present study adopts a realistic initial sample size aimed at (i) quantifying the signal of efficacy and its heterogeneity across subgroups, (ii) evaluating feasibility, adherence, and safety, and (iii) providing empirical estimates of variance, correlation, and attrition rates to inform a subsequent definitive trial with higher precision. Should recruitment capacity allow, the sample may be progressively expanded to narrow confidence intervals around clinically meaningful differences of 8–10 points.

Furthermore, feasibility expectations regarding adherence and dropout are informed by a previous pilot study conducted in 2023 at GUPES. Based on this experience, we anticipate an adherence rate of approximately 60–70% in the current RCT, with an expected dropout rate of around 25%. Dropout is primarily anticipated among participants undergoing active cancer treatment, who may experience treatment-related side-effects or changes in medical status that prevent continued participation.

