During all supervised training sessions, participants will be continuously monitored by certified fitness instructors. Clear criteria for temporary exercise cessation will be applied, including, but not limited to, chest pain, dizziness, excessive dyspnoea, abnormal fatigue, nausea, musculoskeletal pain, or any symptom perceived as alarming by the participant or instructor. In such cases, exercise will be immediately stopped, vital signs will be assessed, and the participant will be referred for medical evaluation when indicated.

Criteria for discontinuation from the intervention will include medical contraindications identified by the treating physician, significant worsening of clinical status, serious adverse events related to exercise, or participant withdrawal of consent. All adverse events will be documented and classified according to severity and relatedness to the intervention.

Importantly, as this study is designed as a feasibility-oriented RCT, safety outcomes (including adverse events, reasons for missed sessions, temporary exercise interruption, and withdrawal) will be treated as key feasibility indicators. These data will inform the refinement of safety protocols and stopping rules in subsequent larger-scale trials.

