### 2.14. Statistical Analysis

Descriptive statistics will summarize baseline characteristics. Primary analyses will follow the intention-to-treat (ITT) principle. To evaluate changes across time points (baseline, 8 weeks, 16 weeks, follow-up), a mixed-effects model for repeated measures (MMRM) will be applied with random intercepts for participants and fixed effects for group, time, and group × time interaction, adjusting for relevant covariates (baseline value, age, sex, treatment status). A covariance structure such as compound symmetry or AR(1) will be selected based on model fit.

For outcomes with only two time points or in case of convergence limitations due to sample size, ANCOVA models adjusted for baseline values will be used as a complementary approach. Effect sizes (Hedges’ g) and 95% confidence intervals will be reported to prioritize estimation over strict hypothesis testing, in line with the feasibility nature of the study. Missing data will be handled using maximum likelihood estimation within the mixed-model framework, and complete-case or multiple-imputation sensitivity analyses will be performed when appropriate. Exploratory moderator analyses (e.g., treatment status, cancer type, adherence) will be reported descriptively. Data will be analyzed using IBM SPSS Statistics (version 29) and Stata (version 18). All tests will be two-sided with α = 0.05.

Given the pilot and feasibility-oriented nature of the study, formal correction for multiple comparisons is not planned. Secondary and exploratory outcomes will be interpreted with caution, emphasizing estimation, variability, and hypothesis generation rather than confirmatory statistical inference.

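### Every missing-data analysis named for the primary outcome relies on missing at random or something stricter, although the dropout the protocol expects may be related to unseen quality of life

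*Protocol article*

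**What the plan says.** The sample-size section (2.6) plans recruitment "with an expected dropout rate of around 25" per cent. It expects the loss mainly among patients on active treatment, "who may experience treatment-related side-effects or changes in medical status that prevent continued participation". It gives no split by arm.

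Section 2.10 makes health-related quality of life the only primary outcome, measured by the QLQ-C30 at baseline, 8 weeks, 16 weeks and follow-up. Section 2.6 frames the target on the global health status/QoL scale: "between-group differences of approximately 8–10 points", with "standard deviations around 20–30 points".

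Section 2.14 plans an intention-to-treat mixed model adjusted for baseline value, age, sex and treatment status. Missing data are handled by maximum likelihood, and "complete-case or multiple-imputation sensitivity analyses will be performed when appropriate". No shift, reference-based rule or pattern-mixture model is named.

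Section 2.12 has a related rule about treatment rather than assessment: "Criteria for discontinuation from the intervention will include medical contraindications identified by the treating physician, significant worsening of clinical status".

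**The concern.** The mixed model and ordinary multiple imputation are valid if the missing scores can be predicted from what was observed: earlier scores, treatment status and the other covariates. Complete-case analysis needs a stricter condition, namely that loss is unrelated to the outcome given the covariates alone. The reasons Section 2.6 gives for dropout are changes in health, and the QLQ-C30 measures functioning and symptoms. A patient who deteriorates between visits and leaves may have an unseen score worse than the earlier data predict.

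None of the named analyses varies that assumption. If the three estimates agree, a reader may take the result as robust when the assumption has not been tested. The wording also allows a complete-case run alone, or no sensitivity analysis if none is judged appropriate. At stake is the size of the efficacy signal, which Section 2.6 lists first among the aims and which is meant to inform a definitive trial.

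**Working it through.** **The plan's own figure.** "The study was pragmatically powered with n = 20 participants per group", at "two-sided α = 0.05 and a nominal power of 80" per cent. With n = 2(1.96 + 0.842)² SD²/d² per group:
- d = 10, SD = 20: 2 × 7.85 × 4 = 63
- d = 8, SD = 30: 2 × 7.85 × 14.06 = 221

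So 20 per group gives about 35% and 13% power, unadjusted. A figure near 20 appears only with high, unstated correlations (for example d = 8, SD = 20, ANCOVA with correlation 0.9: 19). Section 2.6 concedes that a confirmatory trial would need far more, and the present point does not rest on this figure. At 25% dropout, 40 × 0.75 = 30 participants remain.

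**Bias formula.** Let p be the fraction missing in an arm and g the points by which a missing-at-random prediction exceeds the true mean of those missing. Then

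bias in the difference = p(exercise) × g(exercise) − p(control) × g(control).

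- Exercise arm affected alone, p = 0.25: g = 0, 10, 20 gives 0, 2.5, 5 points. Against the target, 2.5/10 = 25% and 5/8 = 63%.
- Same p and same g in both arms: the terms cancel and the bias is zero.
- The sign reverses if the control arm's term is the larger.

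The values of g are assumptions; the protocol gives none.

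**Simulation check.** 400,000 simulated patients were used, so that differences reflect bias and not noise. Assumptions: SD 25, true week-16 difference 8, correlation 0.6 between visits, half the patients on treatment, dropout after week 8. The overall loss is 25% in every row. The 35/15 and 40/10 splits (exercise/control, %) are assumptions. Estimated week-16 difference:

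| Dropout depends on | Split | Full data | Maximum likelihood | Complete-case | Imputation, no shift |
|---|---|---|---|---|---|
| Treatment status only | 25/25 | 8.07 | 8.03 | 8.01 | 8.04 |
| Treatment status only | 35/15 | 8.04 | 8.06 | 8.05 | 8.09 |
| Treatment status only | 40/10 | 7.99 | 7.98 | 7.99 | 7.94 |
| Treatment status and week-8 score | 25/25 | 7.97 | 7.91 | 7.93 | 7.90 |
| Treatment status and week-8 score | 35/15 | 7.89 | 7.85 | 9.21 | 7.87 |
| Treatment status and week-8 score | 40/10 | 8.10 | 8.10 | 10.11 | 8.10 |
| Treatment status and unseen week-16 score | 25/25 | 7.97 | 7.97 | 7.94 | 7.92 |
| Treatment status and unseen week-16 score | 35/15 | 7.96 | 11.03 | 11.46 | 11.05 |
| Treatment status and unseen week-16 score | 40/10 | 8.06 | 12.70 | 13.37 | 12.74 |

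The formula reproduces the last two rows. The simulated gaps g were 17.1 (exercise) and 19.4 (control) at 35/15: 0.35 × 17.1 − 0.15 × 19.4 = 3.1. At 40/10 they were 16.8 and 20.3: 0.40 × 16.8 − 0.10 × 20.3 = 4.7.

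In those two rows the three planned methods lie within 11.46 − 11.03 = 0.4 and 13.37 − 12.70 = 0.7 points of each other. All are too high, by about 3 to 5 points.

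**What a shift would show.** Lowering the imputed values of all dropouts by 5, 10, 15 and 20 points gives 10.1, 9.1, 8.0 and 7.0 at 35/15, and 11.3, 9.8, 8.3 and 6.8 at 40/10. The same shift in both arms moves the difference only by shift × (p exercise − p control), so at equal loss it does nothing. That is why a shift in the exercise arm alone is also needed.

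**The case against.** - **Bias needs two conditions that the protocol does not state.** Loss must depend on unseen scores, and its effect must differ between arms. The table shows about zero bias at equal loss. It also shows none in maximum likelihood or imputation when dropout follows treatment status or the week-8 score. This stands, and is why the range starts at 0. A different loss by arm is plausible, since only the exercise arm trains three times a week, but every entrant must commit to that schedule (Table 1).
- **A reader might infer that the text anticipates bias, or contradicts missing at random within treatment status.** It does neither. Section 2.6 anticipates dropout and gives reasons; treatment status is in the model, and decline visible at earlier visits is used.
- **A reader might take the discontinuation criteria in Section 2.12 as evidence of missing outcomes.** They concern stopping the intervention. Section 2.9 schedules four assessments for each participant, and nothing says these end when training does.
- **Complete-case is not useless.** When loss follows the week-8 score it moves to 9.2 or 10.1 while maximum likelihood stays near 8, so the planned checks need not always agree.
- **Imputation detail belongs in an analysis plan, and imputation can carry a shift.** In part this stands. But Section 2.14 itself chooses the sensitivity analyses and states no shift, so the criticism is of a choice made there.
- **This is a small estimation pilot.** With 15 completers per arm the unadjusted standard error is SD × √(2/15), or 7.3 to 11.0 points for SD 20–30 (95% half-width about 14 to 21 with 1.96). A bias of 5 points is under one standard error. That limits the priority, and an elaborate set of sensitivity analyses would be too much. It does not make the named checks informative about the assumption.

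**Conclusion.** The point holds in a limited form. The main analysis and the named sensitivity analyses all rely on missing at random or stricter, while the expected reasons for dropout may be related to unseen quality of life. Agreement among these analyses would not show whether the QLQ-C30 result depends on the assumption.

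The possible bias is roughly 0 to 5 points against an 8–10 point target. The upper part of that range rests on assumed splits by arm and assumed gaps between true and predicted scores. The documents do not support the stronger reading that the benefit will be overstated. They support only that the plan could not tell. The consequence is modest, because the trial is an estimation-focused pilot, but the estimate is meant to feed a larger trial and the remedy is cheap.

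**What to change.** In Section 2.14, for the QLQ-C30 global health status/QoL scale:

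1. Specify the multiple-imputation sensitivity analysis as delta-adjusted over a stated range, for example 0 to −20 points, once in the exercise arm alone and once in both arms. Report how the estimate and its confidence interval move.
2. Report dropout and its reasons by arm beside that analysis.
3. Keep complete-case analysis, if wanted, as a secondary check.
4. State that QLQ-C30 collection continues after training stops, where the participant agrees, and that these scores enter the intention-to-treat analysis.

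The cost is a few extra analysis runs and a possibly less favourable range of estimates. Item 4 may also need some practical arrangement. Section 2.10 allows digital or paper completion, but Section 2.12 places all assessments at one site, so remote completion cannot be taken as already planned. Reference-based imputation on top of this is more than a 40-person pilot needs.

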### 2.15. Expected Results

We expect that participation in the Onco-Move programme will lead to improvements in key psychophysical outcomes, including health-related quality of life, emotional well-being, stress-response strategies, and physical functioning. We also anticipate positive adaptations in neuromuscular performance, functional fitness, balance, cardiorespiratory capacity, and body composition. Furthermore, physiological changes are expected in markers of inflammation, metabolism, muscle remodelling, and cellular ageing, reflecting the biological impact of structured exercise.

Regarding nutrition, although no dietary intervention is included, adherence to the Mediterranean diet will be assessed before and after the programme using the MEDAS questionnaire. This will allow us to adjust for any incidental changes in dietary habits that could influence the effects attributed to exercise. At the same time, collecting this information will enable exploratory cross-sectional analyses examining how Mediterranean diet adherence relates to other dimensions measured in the project—such as functional fitness, inflammatory biomarkers, psychological health, and overall quality of life. These analyses may provide additional insight into the broader lifestyle context influencing the health of people living with and beyond cancer.

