## Abstract

Despite evidence that exercise improves treatment outcomes, most people living with and beyond cancer (PLWBC) are insufficiently physically active. To address this challenge the Onco-Move Improvement of psychophysical fitness in adult cancer survivors pilot randomized controlled trial aims to investigate the 7-month effects of a 16-week supervised, multicomponent exercise programme on PLWBC adults aged 18–55. The study will include 40 participants currently undergoing cancer treatment or up to 5 years post-treatment with different types of cancer, who will be randomly assigned to the experimental or the control group. The exercise programme will take place three times a week for 16 weeks. We hypothesize that the Onco-Move exercise programme will improve participants’ quality of life, sexual function, and stress-response strategies, as well as their nutrition, physical functions, and body composition. We also expect to observe physiological changes related to the intervention influencing inflammation, metabolism, muscle adaptation, and cellular aging. The Onco-Move exercise programme, once validated, has the potential to be implemented in oncological non-governmental organizations (NGOs) and hospitals in Poland and Spain, among others, as a feasible, effective, and safe non-pharmacological aid for cancer patients and survivors.

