Despite evidence that exercise improves treatment outcomes, PLWBC do not follow these recommendations. A total of 36.7% of cancer survivors aged 18 years and older do not perform any physical activity [11], and up to 93% report insufficient physical activity in their leisure time [12]. Some contributing factors include a lack of time, motivation, and self-discipline and also a lack of personalized exercise programs [12].

To address these challenges, the Onco-Move pilot randomized controlled trial aims to investigate the 7-month effects of a 16-week supervised, multicomponent exercise programme on adults aged 18–55 living with or beyond cancer. The results of this study may help to assess the effectiveness of exercise as a therapeutic component of health-related quality of life (HRQoL), functional fitness, body composition, nutrition, and other factors described later in this publication.

Although no dietary intervention will be implemented, nutrition is considered a core lifestyle dimension within the Onco-Move study. Adherence to the Mediterranean diet will be systematically assessed using the validated MEDAS questionnaire, not only as a control variable but also as a relevant lifestyle factor that may interact with exercise-related adaptations in PLWBC. This feasibility-oriented, observational approach allows for the exploration of diet–exercise interactions in real-world conditions, providing preliminary insight to inform future combined exercise–nutrition interventions.

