### 2.12. Interventions

The Onco-Move exercise intervention is planned according to the CERT. The programme is based on the Individualized and Progressive Health Model [36] (presented in Figure 3.: Onco-Move Individualized and Progressive Health Model) and will include different types of exercises covering all the fitness components (cardio, strengthening, balance, shaping exercises, and stretching). The Individualized and Progressive Health Model (IPS) is a conceptual framework described in a technical monograph [36] and grounded in established exercise prescription principles widely supported by peer-reviewed exercise oncology guidelines.

Participants will perform exercises without any equipment, whereas specific exercises will be performed with such equipment as sports rubber bands, sensory-motor discs, Pilates balls, dumbbells, and cycle ergometers.

All training sessions will be conducted in fitness studios and the gym at Gdansk University of Physical Education and Sport by four certified professional fitness instructors, who will be additionally trained by a certified cancer exercise specialist, and the entire exercise program will be supervised by an expert exercise physiologist with experience in exercise interventions. The in-person interventions will be provided to a group of 20 participants.

The instructors who will supervise exercise performance will correct exercise techniques, ensure the participants maintain the correct movement pattern, provide guidance, provide feedback, and modify exercises as required by a specific type of cancer and treatment.

Adherence will be measured by the percentage of the Onco-Move training sessions completed, defined as the number of the training sessions attended divided by the total number of the training sessions delivered. The reason for absence from training (caused by the treatment regimen, side-effects of treatment, infections, and other reasons) will be reported by patients completing the post-training assessment form (an online tool created by the research team on the Google Forms platform). This approach will allow for feasibility to be evaluated under real-world conditions and provides critical information on barriers that cannot be fully eliminated within the scope of the current study.

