**Secondary outcomes**				
Other quality-of-life variables ^2^	x	x	x	x
Functional fitness ^3^	x	x	x	x
Body composition ^4^	x	x	x	x
Self-reported physical fitness (IFIS)	x	x	x	x
Postural stability and balance control	x	x	x	x
Neuromuscular function	x	x	x	x
Cardiopulmonary fitness	x	x	x	x
Lower limb power and force	x	x	x	x
Grip strength	x	x	x	x
Blood lactate levels	x		x	
Biochemical markers ^5^	x		x	
Genetic analysis ^6^	x			
Nutritional assessment	x	x	x	x
Telomeres and telomerase	x		x	
Post-training assessment ^7^	x	x	x	

^1^ EORTC QLQ-C30. ^2^ Female Sexual Function Index (FSFI), International Index of Erectile Function (IIEF), UWIST Mood Adjective Checklist (UMACL), The Feeling of Stress Questionnaire (KPS), Four-Item Patient Health Questionnaire For Anxiety And Depression (PHQ-4), NEO Five-Factor Inventory (NEO-FFI), and State–Trait Anxiety Inventory (STAI). ^3^ Senior Fitness Test (SFT), Short Physical Performance Battery (SPPB). ^4^ Inbody 720: body fat (%), fat mass (kg), fat-free mass (kg), bone mass (kg), body mass index (BMI; kg/m2), intra-extracellular water (L), waist-to-hip ratio (WHR). ^5^ IL-6 (Interleukin-6), IL-15 (Interleukin-15), Irisin, BDNF (Brain-Derived Neurotrophic Factor), SPARC (Secreted Protein, Acidic, and Rich in Cysteine), Decorin. ^6^ CE, ACTN3, PPARGC1A, BDNF, VEGF, IL6, NOS3, HIF1A, TNF-α, mTOR pathway, telomeres, and telomerase. ^7^ Online post-training assessment forms filled out by the participants up to 24 h after each training session.

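### Section 2.15 says the exercise effect will be adjusted for diet change measured after randomisation, which conflicts with the intention-to-treat model in Section 2.14

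*Protocol article*

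**What the plan says.** The protocol article gives diet several roles.

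- **Adjustment variable.** Section 2.15 (Expected Results) states that "adherence to the Mediterranean diet will be assessed before and after the programme using the MEDAS questionnaire" and continues: "This will allow us to adjust for any incidental changes in dietary habits that could influence the effects attributed to exercise". The Introduction describes MEDAS as used "not only as a control variable but also as a relevant lifestyle factor that may interact with exercise-related adaptations".
- **Outcome.** Section 2.10 lists Mediterranean diet adherence among the secondary outcomes, and Table 2 schedules the nutritional assessment at all four visits.
- **Expected benefit.** The Abstract hypothesises that the programme will improve quality of life and other outcomes, "as well as their nutrition, physical functions, and body composition". Section 4 (Conclusions) asks whether participants will change their diet of their own accord during the project.

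Section 2.14 (Statistical Analysis) is the only place that specifies a model. Primary analyses are by intention to treat. The mixed model has group, time and their interaction, with baseline value, age, sex and treatment status as covariates. Diet is not among them, and Section 2.11 (control variables) does not list it either.

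On adherence, Section 2.14 says: "Exploratory moderator analyses (e.g., treatment status, cancer type, adherence) will be reported descriptively". Section 2.12 says: "Adherence will be measured by the percentage of the Onco-Move training sessions completed", that is, sessions attended over sessions delivered.

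**The concern.** An intention-to-treat comparison estimates the total effect of being allocated to the programme, including any part that arises because participants in the exercise arm start to eat differently. A change in diet during the programme may be a consequence of allocation. Calling it incidental assumes that it is not, while the Abstract predicts that it is.

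Adjusting for it can do two things. It removes the part of the effect that passes through diet. And where something unmeasured, such as motivation or general health, drives both diet and quality of life, holding diet change fixed makes the arms differ on that unmeasured factor. Both need allocation to move diet.

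Section 2.10 makes quality of life the sole primary outcome, and Section 2.6 says the pilot is meant to quantify the signal of efficacy and inform a definitive trial. With Sections 2.14 and 2.15 as written, two different estimates of that signal are available, and no rule says which one stands.

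**Working it through.** **The texts side by side.** Section 2.14 fixes a model with no diet term, while Section 2.15 announces an adjustment for diet change without naming an outcome, model or tier of analysis. MEDAS change uses a value taken after randomisation, whether the schedule is the before-and-after one in Section 2.15 or the four visits in Table 2.

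**Size.** The plan gives no figure for this adjustment, so there is none to reproduce. Two inputs come from Section 2.6: a between-group difference of 8–10 points (midpoint 9) and an SD of 20–30 points (midpoint 25), with 20 per arm. The rest are assumptions, because the document gives no data on MEDAS:

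- *a*: shift in diet change caused by allocation, in within-arm SDs of diet change (0, 0.25 or 0.5)
- *b*: quality-of-life points per SD of diet change (0 or 5)
- *g*: correlation of an unmeasured shared cause with diet change (0 or 0.5)
- *h*: quality-of-life points per SD of that shared cause (0 or 10)

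The within-arm slope of quality of life on diet change is *b* + *g·h*. In a linear model, therefore:

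adjusted effect = total effect − *a* × (*b* + *g·h*)

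A least-squares simulation (one follow-up value, 20 per arm, 5,000 replicates) was run alongside.

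| Scenario | *a* | *b* | *g* | *h* | Formula | Simulated, without diet term | Simulated, with diet term |
|---|---|---|---|---|---|---|---|
| Diet matters, allocation does not move it | 0 | 5 | 0 | 0 | 9 − 0 = 9.0 | 9.00 | 8.95 |
| As above, plus shared cause | 0 | 5 | 0.5 | 10 | 9 − 0 = 9.0 | 8.94 | 8.94 |
| Small shift, diet matters | 0.25 | 5 | 0 | 0 | 9 − 1.25 = 7.75 | 9.01 | 7.72 |
| Larger shift, diet matters | 0.5 | 5 | 0 | 0 | 9 − 2.5 = 6.5 | 8.86 | 6.36 |
| Larger shift, shared cause only | 0.5 | 0 | 0.5 | 10 | 9 − 2.5 = 6.5 | 8.83 | 6.33 |
| Larger shift, both | 0.5 | 5 | 0.5 | 10 | 9 − 5 = 4.0 | 9.05 | 4.08 |

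The simulated means carry a Monte Carlo error of about 7.9/√5000 = 0.11 and agree with the formula within that error. Attenuation runs from 0% (*a* = 0) to 5/9, about 55%.

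The term multiplying the bias is *a*. With *a* = 0 the estimate is unbiased even when diet matters and a shared cause exists. For scale, the standard error of one trial's estimate here is about 25 × √(2/20) = 7.9 points, so the shift would be hard to see in a single data set, but it is systematic.

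**Adherence.** By the Section 2.12 definition, a control participant has no sessions to attend, and Section 4 confirms that controls do not take part in the programme. Adherence therefore has no value in one arm, and an interaction of arm with adherence cannot be estimated.

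**The case against.** The strongest reply is that the analysis section is sound. Section 2.14 specifies intention to treat and omits diet. The disputed sentence sits under Expected Results, says only what the data will allow, and does not say the primary estimate will be adjusted or replaced. Control variable in the Introduction could mean baseline MEDAS, which would be harmless. Nutrition as an expected benefit appears in the Abstract but not in the expected improvements of Section 2.15 or the restated hypothesis in Section 4. The trial is a pilot that emphasises estimation, and it includes no dietary intervention, so a large diet shift is not a given.

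Most of that stands, and it rules out several stronger readings:

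- A reader might infer that the primary quality-of-life analysis is already adjusted for diet change. It is not; the specified model contains no such term.
- A reader might infer that shared causes of diet and quality of life bias the comparison in any case. They do so only if allocation shifts diet; otherwise randomisation protects the comparison.
- A reader might infer that the adherence analysis biases the main result, or that the plan claims a dose-response relation. The analysis is exploratory and descriptive, does not enter the intention-to-treat model, and no section proposes dose-response.

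The reply does not dispose of the Section 2.15 sentence itself. That sentence names changes in diet, not baseline diet, and its stated purpose is to correct the effect attributed to exercise. This is a stated adjustment that contradicts another section, so it is more than a detail left to an analysis plan.

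**Conclusion.** The point holds as a conflict between Section 2.15 (with the Introduction) and Section 2.14. The adjustment announced in Section 2.15 would not estimate the total effect of allocation if the programme changes diet, which the Abstract expects. The illustrated attenuation of a 9-point effect runs from none to about 55%. That range rests on assumed values for the diet shift, the diet effect and the shared cause, and on a linear model with one follow-up; the document supports no narrower figure. Nothing here shows that the Section 2.14 model is biased.

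The adherence point is separate and minor. Moderator is the wrong label for a quantity defined in one arm, and the intention-to-treat estimate is unaffected.

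**What to change.** 1. Keep the Section 2.14 model as specified, with no diet term measured after randomisation.
2. If diet is to be a covariate, use baseline MEDAS only, name it in Section 2.14, and say in the Introduction that control variable means the baseline value.
3. Analyse change in MEDAS as a secondary outcome, by arm.
4. Strike the Section 2.15 sentence on adjusting for incidental changes, or relabel it as an exploratory mediation analysis, with its assumptions stated, that never replaces the intention-to-treat estimate.
5. Remove adherence from the list of moderators in Section 2.14 and describe it within the exercise arm, with the reasons for absence that Section 2.12 already collects. No complier-average analysis is needed.

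The cost is wording only. No new data, visits or participants are required.
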